#### *Incident STIs (Aim #3)*

Analyses of incident STIs will evaluate all STIs tested throughout the study. GLMM will be used, and we will follow the similar procedure outlined in Aim #2.

### Secondary analyses

#### *STI and pregnancy risk behaviors*

For this analysis we will utilize the TLFB data to identify the percentage of at-risk days that women engage in sexual activity not protected against an unplanned pregnancy. We will include use of all coital and non-coital contraceptive methods in this analysis, as well as sexual activity without a condom (not protected against STIs). GLMM will be used to test this hypothesis, and we will follow the similar procedure outlined in Aim #2.

#### *Predictors of contraceptive use*

Predictive variables will include demographics of age, race/ethnicity, and education as well as drug and alcohol use, depression, recent and childhood victimization, and pregnancy history. Following the stages of change, decisional balance, process of change, and self-efficacy will allow for an in-depth evaluation of the intervention. By following changes in these processes, the components of the intervention which most affect behavioral change can be determined.

Alternatively, we will also use measurement modeling to incorporate multiple measures, such as the self-reported primary outcomes and the incidence of pregnancy and STI in a latent factor that captures variance common to all measures
[40]. Statistical analyses with latent variables allow us to minimize measurement error and thereby increase validity of the study.

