**Methods/Design:**

This randomized controlled trial will recruit 400 women from the Rhode Island Department of Corrections (RI DOC) women’s jail at risk for an unplanned pregnancy (that is, sexually active with men and not planning/wanting to become pregnant in the next year). They will be randomized to two interventions: a control group who receive two educational videos (on contraception, STIs, and pre-conception counseling) or a treatment group who receive two sessions of personalized MICA. MICA is based on the principles of the Transtheoretical Model (TTM) and on Motivational Interviewing (MI), an empirically supported counseling technique designed to enhance readiness to change targeted behaviors. Women will be followed at 3, 6, 9, and 12 months post release and assessed for STIs, pregnancy, and reported condom use.

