### Procedures/Interventions

A research assistant (RA) will recruit potential participants in the housing units at the RI DOC. She will identify herself as non-RI DOC staff and inform women that study participation is completely voluntary and will not affect any privileges at the facility. Individuals who are interested in participating will be given an informed consent form to review and the study will be explained. Given that incarcerated populations are vulnerable populations with limited rights, the informed consent process is particularly important. The RA will detail that study participation is not linked to any extra medical or non-medical services in prison and will not influence parole status or any other jail privileges. Additionally, it will be explained that she does not need to participate in the study to receive reproductive health services. It will be explained that this is a confidential study but that if there is any information that a participant may harm herself, another person, or that a child or an elderly or disabled individual is in danger then that information will be reported. If there is a threat made to the security of the prison then prison staff will be informed. Counselors are instructed not to discuss study participation with any one at the RI DOC. All study staff are certified through the hospital in Human Subjects Protection and HIPAA, and a certificate of confidentiality has been obtained to further insure participant confidentiality.

Inclusion and exclusion criteria will be reviewed. If eligible and willing to participate in the study, the informed consent process will be completed (study explained, consent form read to the individual, and questions answered) and forms signed. Locator information will be obtained and consents signed for tracking
[35].

Participants will be randomized by age (25 years or younger *vs*. older than 25 years), race/ethnicity (non-Hispanic White *vs*. other), and pregnancy intentions (wants no more pregnancies *vs*. wants a future pregnancy). Future pregnancy plans will be assessed by a single question: ‘Do you want to have any/anymore children?’ Based on these criteria there will be eight randomization groups. A random number generator will determine intervention status for the eight groups. Intervention status is then placed into sequentially numbered envelopes for the eight groups and each envelope is sealed and opened in order as women become eligible in each of the eight groups.

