#### *MICA*

Participants randomized to MICA will receive all core MI elements in the MICA sessions. A key component of any MI-based intervention is for the counselor to support autonomy by explicitly stating that it is the participant, not the counselor, who will make decisions regarding behavior change. Counselors will lead the participant in a directed, empathic discussion that includes a review of the Timeline Followback (TLFB) calendar, pregnancy intentions, the pregnancy and STI risk assessment printouts, and Stages of Readiness to Change. The behaviors targeted vary depending on the needs of the participant with the overall goal of decreasing the risk for unplanned pregnancies and STIs. For example, some want to focus on decreasing the number of sex partners, some using birth control consistently, and others want to see a medical provider to initiate a birth control method. The counselor will support the participant’s decision to make, or consider the possibility of, change. All MICA participants will receive: (1) feedback on personal risks for pregnancy and STIs; (2) clear advice to avoid pregnancy (until it is desired) and STIs that might impact future fertility by either using highly effective contraceptives and condoms consistently and correctly or staying abstinent; and (3) a review of the menu of options by which to prevent pregnancy and STIs. Detailed education about contraceptive choices is offered according to the participant’s needs and requests. The session will end with the development of a ‘CARE plan’ in which the participant lists her goals and methods for reaching her STI and pregnancy prevention goals. A second MICA session will be conducted 3 months after release and include a review of the’CARE plan’ as well as elements provided in session one. If a woman chooses no method or decides she wants to become pregnant then preconception counseling is offered.

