#### *Treatment fidelity*

To promote treatment integrity, all treatment sessions will be audio-recorded and reviewed weekly by the treatment supervisor, who will use a MICA adherence checklist to assess session content and process as well as the MITI 3.1.1 scale to assess the quality of MI at each session
[41,42]. Prior to enrolling participants, counselors will receive individualized feedback and coaching by a treatment supervisor who has reviewed every audio-recorded MICA sessions until the counselors are certified to competently conduct MICA counseling. Then counselors will receive feedback and coaching for the first 10 audio-recorded MICA sessions and over time will be provided with written feedback and coaching for every other to every third audio recordings. To insure fidelity an independent reviewer will code 10% of all coded MICA sessions using the Motivational Integrity Treatment Integrity scale. A counselor who falls below acceptable levels of proficiency in MICA will be identified and re-trained until able to demonstrate the necessary knowledge and skills.

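### The plan says that following process measures will determine which MICA components work, but no component is randomised, so only the whole-package effect is identified

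*Protocol article*

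**What the plan says.** The claim stands in the protocol article under Secondary analyses, Predictors of contraceptive use. The article first says: "Following the stages of change, decisional balance, process of change, and self-efficacy will allow for an in-depth evaluation of the intervention". It then concludes: "By following changes in these processes, the components of the intervention which most affect behavioral change can be determined". The conclusion is unqualified. It is not called exploratory, and no model or assumption accompanies it.

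Other sections fix what the design can support:

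- **Arms.** The abstract describes two: "They will be randomized to two interventions: a control group who receive two educational videos", and a treatment group given two MICA sessions.
- **Randomisation.** Procedures/Interventions says: "A random number generator will determine intervention status for the eight groups". Those groups are strata formed by age, race/ethnicity and pregnancy intentions. They are not versions of MICA.
- **Content common to the MICA arm.** "Participants randomized to MICA will receive all core MI elements in the MICA sessions". The same section lists personal risk feedback, clear advice and a menu of options as given to all MICA participants.
- **Content that varies within the MICA arm.** "The behaviors targeted vary depending on the needs of the participant with the overall goal of decreasing the risk for unplanned pregnancies and STIs", and "Detailed education about contraceptive choices is offered according to the participant’s needs and requests". Preconception counselling is offered to women who choose no method or decide that they want a pregnancy.
- **Delivery data.** Under Treatment fidelity, recorded sessions are reviewed by a supervisor "who will use a MICA adherence checklist to assess session content and process". The stated purpose is treatment integrity.

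**The concern.** The sentence moves from processes to components without a link between them. Readiness, decisional balance and self-efficacy are states of the participant, while components are things that the counsellor delivers. One state may respond to several delivered elements, and the design never gives one core element without the others.

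If the plan is followed as written, an association between a process score and contraceptive use would be reported as evidence on which part of MICA works. Such an association can arise from a common cause, or in reverse, since starting a method may itself raise self-efficacy. A later programme that kept or dropped counselling elements on that basis would be relying on a conclusion that the trial was not built to support.

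**Working it through.** The plan attaches no figure to this claim. Its one design figure, 400 women (200 per arm) for incident STI, is not in question here. The check is one of identifiability.

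**1. The randomised comparison.** Take the three elements that the MICA section gives to every MICA woman: feedback, advice and menu of options. Let c1, c2 and c3 indicate receipt of each, and let A = 1 for MICA and 0 for video. Treat the elements as absent under video, which is the most favourable coding for the claim. Then c1 = c2 = c3 = A for all 400 women, and the model

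mean outcome = b0 + b1·c1 + b2·c2 + b3·c3

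reduces to b0 + (b1 + b2 + b3)·A.

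The 400 × 4 design matrix has rank 2. Two quantities are estimable: b0 and the sum b1 + b2 + b3. If the package effect is t, then (t, 0, 0), (0, t, 0) and (t/3, t/3, t/3) all give the same fitted means. More participants would not separate them.

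**2. Variation inside the MICA arm.** Target behaviours, detailed contraceptive education and preconception counselling do differ between women. They differ because of need, request or a decision about pregnancy, and each of these plausibly predicts contraceptive use directly. A comparison of women who did and did not receive such content is therefore confounded by indication. Fidelity records could describe what was delivered, but they would not remove this confounding, and the sentence rests on process changes, not on delivery records.

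**3. Adding the process measures.** Let M be a process score measured after randomisation. The trial supports an unconfounded estimate of the effect of A on M, provided that M is measured in both arms and losses to follow-up are ignorable. The effect of M on later use is not randomised. An indirect effect of A through M therefore needs the assumption of no unmeasured mediator-outcome confounding. Even where that holds, the result concerns M and does not say which of c1, c2 or c3 moved M.

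**4. Timing.** The second MICA session takes place 3 months after release, and follow-up visits are at 3, 6, 9 and 12 months. A month-3 score taken before that session reflects session 1 only. A month-6 score can reflect both sessions, with month-9 or month-12 use as the later outcome. Initiation in jail precedes every follow-up score, so none of these scores can mediate it.

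**The case against.** The strongest reply is that components is used loosely. MICA is built on the Transtheoretical Model, the four measures are constructs of that kind, and the Background says that motivational interviewing supports self-efficacy and explores pros and cons. On that reading the sentence announces a study of mechanism. It is also one sentence in a condensed article, and a mediation model, its covariates and its timing would normally appear in the full protocol or analysis plan.

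Part of this stands. Missing model detail is no fault here, and a mechanism analysis is reasonable. But the article asserts a conclusion, not merely an intention, and the conclusion names components of the intervention. An unseen plan could add a model, but it could not make the two-arm comparison identify component effects.

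Three stronger readings are tempting, and the documents do not support them:

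- **That content does not vary within MICA.** It does, as the MICA section and the Background show. The correct statement is that none of the variation is randomised.
- **That the arms share nothing.** The video also gives information on contraception and STI prevention, and both arms receive the list of services and the offer of a Title X referral. The coding in step 1 is a simplification in the claim's favour.
- **That the analysis makes no comparison between arms.** The subheading may suggest this, but the article specifies no model either way.

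**Conclusion.** The point holds. The trial has one randomised contrast, MICA as a whole against video, and it carries no randomised information on separate component effects. This is structural and depends on no assumed effect size. It follows from the two arms, the delivery of all core elements to every MICA woman, and the use of post-randomisation participant measures. No numerical bias can be attached, because the documents give no association between process scores and contraceptive use.

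Process measures can still inform mediation of the package effect, under the assumption of no unmeasured mediator-outcome confounding. That assumption is demanding: a method started in jail could both raise a later self-efficacy score and predict continued use. Measuring the process before the outcome reduces this problem but does not remove it.

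A reader might infer that the trial's main results are in doubt. They are not. The claim belongs to a secondary analysis, and the primary comparisons of initiation, continuation and incident STI are unaffected. This is a minor point, worth correcting because the sentence promises a causal conclusion.

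**What to change.** Delete the sentence saying that components can be determined. Replace it with an analysis labelled exploratory that:

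- estimates the between-arm difference in each process measure, and then the indirect effect of allocation on later contraceptive use through it;
- measures the process before the outcome visit, on the same scales in both arms;
- adjusts for the baseline process score and the randomisation factors (age, race/ethnicity, pregnancy intentions);
- states the assumption of no unmeasured mediator-outcome confounding;
- states that a month-3 score taken before the second session reflects session 1 only, and that a month-6 score with month-9 or month-12 use covers both sessions;
- states that initiation in jail is outside this analysis;
- limits conclusions to processes, not components.

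The cost is a weaker stated claim and modest extra analysis. The article does not say whether the scales are given to both arms. If they are not, some questionnaire items must be added. Randomisation, sample size and the primary analyses stay as they are.

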#### *Treatment fidelity*

To promote treatment integrity, all treatment sessions will be audio-recorded and reviewed weekly by the treatment supervisor, who will use a MICA adherence checklist to assess session content and process as well as the MITI 3.1.1 scale to assess the quality of MI at each session
[41,42]. Prior to enrolling participants, counselors will receive individualized feedback and coaching by a treatment supervisor who has reviewed every audio-recorded MICA sessions until the counselors are certified to competently conduct MICA counseling. Then counselors will receive feedback and coaching for the first 10 audio-recorded MICA sessions and over time will be provided with written feedback and coaching for every other to every third audio recordings. To insure fidelity an independent reviewer will code 10% of all coded MICA sessions using the Motivational Integrity Treatment Integrity scale. A counselor who falls below acceptable levels of proficiency in MICA will be identified and re-trained until able to demonstrate the necessary knowledge and skills.

## Discussion

The United States female jail population is a large population, particularly among women of childbearing age. Women leaving jail are at high risk for unplanned pregnancies and STIs and face many barriers to reproductive health services such as lack of insurance, transportation issues, and child care issues
[43-47]. This research project is a RCT of an experimental intervention for incarcerated women at risk for unplanned pregnancies and STIs. It will compare changes in the initiation and maintenance of highly effective contraceptives and STI risk behaviors at multiple time points up to 12 months after release from the incarcerated setting. Improving contraceptive service utilization in this non-traditional setting has the potential to reach the women in the greatest need of services.

## Trial status

Recruitment for this trial is ongoing and expected to end by September 2012.
